## 11. STATISTICAL CONSIDERATIONS

### 11.1 STATISTICAL PROCEDURES AND DATA ANALYSIS

#### 11.1.1 Primary Effectiveness: Definition of Success (or Failure) of the Endpoint

The time to first suicide attempt after randomization is the primary endpoint. The study will be a success if the primary endpoint is statistically significant in favor of Aviva (compared to sham app) based on time to suicide attempt, a time-to-event variable. At 90% power, fifty suicide attempts (i.e., event) are expected while following 391 participants for 104 weeks. In anticipation that treatment effects may be observed before 50 suicide attempts occur, the primary endpoint will be tested via a group sequential test with K = 4 Looks using an O'Brien-Fleming like alpha spending function boundary. A non-binding futility boundary is incorporated in this design, also with an O'Brien-Fleming boundary. The Type I error level alpha will be protected at level 0.025 one-sided (which is equal to 0.05 two-sided).

Study failure will be defined as lack of a statistically significant finding for suicide attempts in favor of Aviva. Details are provided below.

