## 4. STUDY DESIGN

### 4.1 OVERALL DESIGN

This double-blind RCT will evaluate the effectiveness of **Aviva + TAU versus a Sham + TAU** among 391 participants, adult inpatients, who had recent suicidal ideation with intent or suicide attempts. Study participation starts when consent is signed and patients are ready for discharge from an inpatient or emergency unit. Participants and assessors will be blinded to treatment assignment. The study is planned to take a total of 104 weeks from first patient randomized (52 weeks for enrollment, up to 104 weeks for patient follow up). An additional 4 months is planned for study close out. The primary endpoint will be analyzed in a group sequential design with looks at 60%, 75%, 90% and 100% of the expected number of suicide attempts. Overall Type I error (alpha) will be less than 0.025 one-sided.

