the high risk and ethical concerns when doing research on suicide, the site PIs will ensure these two monitoring components are followed: 1) the clinical/safety monitoring of individual participants; 2) review of study data to assure data accuracy and consistency. DSMB members will include individuals who have extensive experience in clinical trials and suicide prevention. Site PIs will monitor data to determine whether study participation is leading to increased risk of harm to subjects by comparing rates and types of harm events across treatment arms. The DSMB will guide our team in assessing the risk of potential liability and matters of safety monitoring. During interim looks at the data for safety, the sponsor will continue to be blinded to condition, as will the assessors. The data will be tabulated by a CRO and forwarded to a DSMB for adjudication. There will be standard operating procedures for the DSMB meetings. Safety events/SAEs are clearly defined elsewhere in the protocol, with stopping rules (see section 11.5 STOPPING RULES). Safety events and SAEs will be reported to the DSMB for review by the DSMB in a timely manner (i.e. within 5 days). The study personnel and sponsor will remain blinded until all enrolled participants have completed the 104 week follow-up. If the DSMB requires the study be stopped (either for SAEs or positive outcomes/benefit), the study will be unblinded and a decision will be communicated to the Sponsor. The sponsor will notify the FDA.

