#### **11.1.3 Justification of sample size-suicide attempts**

Power and sample size calculations were made in nQuery, Version 8.7.2. Initial sample size calculations for suicide attempts were based on Rudd et al. (2015). A total sample size of 391 (with 52 events) is required to achieve 90% power to detect a hazard ratio of 0.3826 (for survival rates of 0.9240 in the Aviva group [group 1] and 0.8124 in sham app group [group 2] at 18 months), using a one-sided log rank test with 2.5% significance level (i.e.,  $p = 0.025$ ) assuming that the survival rates are exponential and that the total study time is 104 weeks (24 months) with 52 weeks (12 months) accrual.

These results assume that the group sequential design has 3 interim sequential tests (4 total looks including final analysis). The O'Brien-Fleming spending function is used to determine the effectiveness test boundary. See Attachment C: Power Calculation and Group Sequential Design for Aviva Trial – Suicide Attempts (Mathematical Formulations) for full details of sample size calculations.

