#### **11.1.4 Group Sequential Design for Suicide Attempts**

Although the dropouts will not provide the clinical interview information at study end, it will be possible to review hospital records to obtain information regarding suicide attempts by participants (this will be confirmed during informed consent). We will randomize 196 participants to the (Aviva) treatment group and 195 participants to the active control (sham) group and expect to have suicide attempt data for 100% of these participants. We investigated several reasonable variations of the group sequential design and determined that the following is most reasonable. We will test at the 0.025 significance-level (one-sided). The group sequential design has 3 interim sequential tests (4 total looks including final analysis). The looks will occur when 60%, 75%, 90% and 100% of the expected events (i.e., suicide attempts) have occurred. The O'Brien-Fleming spending function is used to determine the effectiveness test boundary. The group sequential design boundaries (on a z scale) are presented in Attachment C.

The power of this GSD is 90%.

Survival analyses will be conducted using the log-rank test for the effectiveness of the intervention on the time to the first suicide attempt after randomization while controlling for censoring effects due to the differential length of follow-up or the completion of follow-up without a suicide attempt. Time to suicide attempt will be measured by calculating the total number of days from enrollment to the first suicide attempt. For participants without a suicide attempt, the total number of days since enrollment to the last assessment will be calculated.

While every effort will be made to track suicide attempts (SA), there may be some missing data. Consistent with standard statistical procedures, missing data are included in the time-to-event analysis as censored observations, with the censoring time at the last contact time with the patient (Friedman et al., 2015).

Estimates of participants making at least 1 subsequent suicide attempt before study end and reattempt-free probabilities at any time point will be derived by the Kaplan-Meier method. The

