between-group difference in the proportion of participants making at least 1 repeat suicide attempt by 104 weeks will be evaluated using the asymptotic properties of the Kaplan-Meier estimators of survival probabilities. Although we do not anticipate dropout (because suicide attempt data can be collected via multiple means), this method was chosen to account for dropouts based on the Intent-to-Treat (ITT) principle.

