**PROPRIETARY AND CONFIDENTIAL**

Oui Therapeutics, LLC | [name]

level to detect a hazard ratio of 0.3826 when the group 1 exponential hazard rate is 0.0115 (this gives a group 2 exponential hazard rate of 0.0044). Under these assumptions, the number of events will be 37 and 15 in group 1 and group 2 respectively. The maximum follow-up time for a subject is 24 time units (months) with an accrual period of 12 time units.

These results assume that the group sequential design has 3 interim sequential tests (4 total looks including final analysis). The O'Brien-Fleming spending function is used to determine the effectiveness test boundary. The O'Brien-Fleming spending function is used to determine the non-binding futility boundary.

The drift parameter for this design equals 3.4387. The drift parameter equals the square root of the maximum information level by the log hazard ratio. The ratio of this drift parameter to the drift parameter from the equivalent fixed term design represents the ratio of the sample sizes required for this GST design to that of its fixed term equivalent.

GST Boundaries (Z scale):

Upper effectiveness bounds: 2.6686, 2.3865, 2.1685, 2.0748

Futility bounds: 0.8347, 1.3133, 1.7538, 2.0748

**ATTACHMENT D***TITLE: Mathematical Formulations for Suicidal Ideation*

PASS 2020, v20.0.3 9/10/2020 2:59:16 PM 1

Two-Sample T-Tests Assuming Equal Variance

Numeric Results for an Equal-Variance T-Test \_\_\_\_\_

 $\delta = \mu_1 - \mu_2$ Hypotheses:  $H_0: \delta = 0$  vs.  $H_1: \delta \neq 0$ 

| Power   | N1  | N2  | N   | $\delta$ | $\sigma$ | Alpha |
|---------|-----|-----|-----|----------|----------|-------|
| 0.83582 | 70  | 70  | 140 | 3.8      | 7.6      | 0.050 |
| 0.88160 | 80  | 80  | 160 | 3.8      | 7.6      | 0.050 |
| 0.91559 | 90  | 90  | 180 | 3.8      | 7.6      | 0.050 |
| 0.94043 | 100 | 100 | 200 | 3.8      | 7.6      | 0.050 |

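### Section 11.1.1 expects 50 events where the design uses 52, and a 104-week trial with 52 weeks of accrual cannot follow everyone for 104 weeks

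*Protocol*

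**What the plan says.** **Event total.** Section 11.1.1 states that at 90% power "fifty suicide attempts (i.e., event) are expected while following 391 participants for 104 weeks". Its next sentence motivates the interim looks by the chance of an effect before the 50th attempt. Section 11.1.3 states: "A total sample size of 391 (with 52 events) is required to achieve 90% power". The synopsis gives the same 52. Attachment C splits it into 37 sham and 15 Aviva events and prints the looks at 31.2, 39, 46.8 and 52. The synopsis and section 3.1 make the analysis event-driven.

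**Trial length.** Section 4.1: "The study is planned to take a total of 104 weeks from first patient randomized (52 weeks for enrollment", and the same parenthesis allows up to 104 weeks of follow-up per patient. The synopsis, 11.1.3 and Attachments A and C also assume 24 months in total with 12 months of accrual; Attachment C calls 24 months the maximum follow-up of a subject.

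**Passages that need 104 weeks for everyone.** Section 9.9: "The study personnel and sponsor will remain blinded until all enrolled participants have completed the 104 week follow-up". Section 11.1.1 ties its 50 events to 104 weeks of follow-up of all 391. Section 11.1.4 plans to test the "between-group difference in the proportion of participants making at least 1 repeat suicide attempt by 104 weeks" from Kaplan-Meier estimates.

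**The concern.** The looks and the final analysis are set as percentages of the expected events, and 11.1.1 is the body section that says how many events are expected. A reader working from it would put the first look at 30 events and the last at 50, while one working from Attachment C would use 31.2 and 52. In a pivotal group sequential trial the final trigger should read the same everywhere before the first look.

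The sentence in 11.1.1 also attaches its count to a follow-up scheme that the sample size did not use. Whether people are followed for 52 to 104 weeks or all for 104 weeks decides when the trial ends, when the blind may be lifted, and whether a 104-week comparison has data behind it.

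**Working it through.** **Inputs.** Attachment C: monthly hazards 0.0115 (sham, n = 195) and 0.0044 (Aviva, n = 196), HR 0.3826, accrual 12 months, total 24 months, drift 3.4387, and the printed efficacy and futility bounds. Section 11.1.1: "The Type I error level alpha will be protected at level 0.025 one-sided". Power is 90%. Section 11.1.4 expects attempt data on 100% of participants, so no dropout is applied.

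**1. Reproduce 52 and 391.**
- Fixed-design events (Schoenfeld): 4 × (1.960 + 1.282)² / (ln 0.3826)² = 45.5.
- Group sequential inflation: (3.4387 / 3.2415)² = 1.125, giving 45.5 × 1.125 = 51.2 events.
- Event probability by month T = 24 with uniform accrual over a = 12 months: 1 − (e^(−λ(T−a)) − e^(−λT)) / (λa).
  - Sham: 1 − (0.8711 − 0.7588) / 0.138 = 0.1863, × 195 = 36.3.
  - Aviva: 1 − (0.9486 − 0.8998) / 0.0528 = 0.0760, × 196 = 14.9.
- Sum 51.2. Rounding each arm up gives 37 + 15 = 52.
- N = 51.24 / 0.1312 (mean event probability) = 390.6, so 391.

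The 52 events and the 391 participants both belong to the 24-month schedule.

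**2. Events if all 391 are followed 24 months.** n × (1 − e^(−24λ)):
- Sham 195 × 0.2412 = 47.0.
- Aviva 196 × 0.1002 = 19.6.
- Sum 66.7, about 67. Hazards derived from the 18-month survival rates give 66.8 to 66.9.

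So 50 is neither the 24-month yield nor the yield of 104 weeks each.

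**3. Effect on the primary test.** Drift at D events is √(D/4) × |ln 0.3826|. Simulating the printed bounds, with futility applied:

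| Events | Drift | Power |
|---|---|---|
| 50 | 3.397 | 89.3% |
| 51.2 (design drift) | 3.4387 | 90.0% |
| 52 | 3.464 | 90.4% |

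Looks at 60/75/90% would be 30/37.5/45 for a total of 50, against 31.2/39/46.8 for 52.

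**4. Calendar.** Solving the step 1 formula for T under the design hazards puts the 50th event at about month 23.5 and the 52nd at about month 24.3. Accrual of 52 weeks plus 104 weeks for the last entrant is 156 weeks, about month 36. The release of the blind in section 9.9 would then fall about a year after the 52nd event.

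**5. The 104-week comparison.**
- 104 weeks is 728 / 30.44 = 23.92 months. At a month-24 cut-off, (24 − 23.92) / 12 = 0.7% of participants have been in the study that long, fewer than 3 of 391.
- Under the design hazards the true 104-week difference is 0.2412 − 0.1002 = 0.141.
- Complete follow-up: SE = √(0.2412 × 0.7588 / 195 + 0.1002 × 0.8998 / 196) = 0.037.
- Cut at month 24.3: simulated trials leave about 8 to 10 people at risk at that horizon, and the SE is about 0.06.

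**The case against.** The best defence is that the design is event-driven and Attachment C is explicit. It prints an event count for each look, 11.1.3 and 11.1.4 send the reader there, and the z-bounds belong to information fractions, so they are the same for 50 or 52. The synopsis also says that participants are expected to be followed 104 weeks but that the analysis occurs when the events have occurred. Section 4.1 allows up to 104 weeks, which is coherent when read as 52 to 104 weeks each. The primary test is the log-rank test, with staggered follow-up handled by censoring.

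Much of this stands, and it rules out several stronger readings that a reader might draw:

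- *Three competing totals.* The protocol states two. The 67 is a derived yield under longer follow-up and appears nowhere as a target.
- *Looks that rest on no number.* Attachment C fixes them.
- *An empty 104-week comparison.* Kaplan-Meier uses all earlier follow-up, so the estimate exists but is very imprecise.
- *A maximum that ought to be 67.* The planned 52 events meet the stated 90% power. An event-driven trial normally leaves later events out of its final test, so a larger maximum would be a design preference.

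Two things remain. The number in 11.1.1 is wrong under either schedule. And the event trigger says when the analysis happens, not when follow-up ends, so it reconciles neither section 9.9 nor the 104-week comparison with a 104-week trial.

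**Conclusion.** The point holds, at moderate severity. Section 11.1.1 gives 50 where the design uses 52, and attributes it to a follow-up scheme that would yield about 67. The cost to the primary test is about one point of power (89.3% against 90.4%), about one event at the first look and two at the last; type I error is not affected.

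The two follow-up schemes are incompatible: 104 weeks in total with 52 weeks of accrual gives 52 to 104 weeks each, while section 9.9 needs about 156 weeks. If follow-up ends at about month 24, the 104-week comparison has a standard error of about 0.06 for an expected difference of 0.141, against 0.037 with complete follow-up.

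These figures assume the protocol's own constant hazards, uniform accrual and no dropout. Slower accrual or a different event rate would move the calendar dates, but would not reconcile the passages.

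**What to change.** 1. In 11.1.1, replace both mentions of 50 by 52. Describe 52 as the event maximum of the 24-month schedule with 12 months of accrual, not as the yield of 104 weeks of follow-up for all 391.
2. State one trial length, in one of two ways:
   - **Follow-up ends with the event-driven final analysis.** Correct the blinding sentence in section 9.9, and make the Kaplan-Meier comparison at a horizon that all can reach, for example 52 weeks. On the design hazards the 52nd event falls near month 24.3, so every participant would have at least 12 months.
   - **All are followed to 104 weeks after the 52-event primary analysis.** Change the total duration in 4.1 to about 156 weeks. Label the 24 months in the synopsis, 11.1.3 and the attachments as the expected time of the primary analysis. Make the 104-week comparison once follow-up is complete, and say who may see the 52-event result while section 9.9 still holds the blind.

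The first option costs only wording. The second also costs about a further year of follow-up beyond the 104 weeks in 4.1, which section 9.9 already implies. Neither changes the sample size, the printed bounds or the 52-event maximum.

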#### **11.1.2 Rationale**

It is anticipated that suicide attempts will reflect benefits of Aviva over sham that are discernable at 104 weeks after randomization. A group sequential design is appropriate because it would be prudent to stop the study earlier for significant effectiveness in the case where the time of participants who attempt suicide is significantly less in the Aviva group compared to the sham group (and thus reducing risk of suicide shortly after discharge).

#### **11.1.3 Justification of sample size-suicide attempts**

Power and sample size calculations were made in nQuery, Version 8.7.2. Initial sample size calculations for suicide attempts were based on Rudd et al. (2015). A total sample size of 391 (with 52 events) is required to achieve 90% power to detect a hazard ratio of 0.3826 (for survival rates of 0.9240 in the Aviva group [group 1] and 0.8124 in sham app group [group 2] at 18 months), using a one-sided log rank test with 2.5% significance level (i.e.,  $p = 0.025$ ) assuming that the survival rates are exponential and that the total study time is 104 weeks (24 months) with 52 weeks (12 months) accrual.

These results assume that the group sequential design has 3 interim sequential tests (4 total looks including final analysis). The O'Brien-Fleming spending function is used to determine the effectiveness test boundary. See Attachment C: Power Calculation and Group Sequential Design for Aviva Trial – Suicide Attempts (Mathematical Formulations) for full details of sample size calculations.

#### **11.1.4 Group Sequential Design for Suicide Attempts**

Although the dropouts will not provide the clinical interview information at study end, it will be possible to review hospital records to obtain information regarding suicide attempts by participants (this will be confirmed during informed consent). We will randomize 196 participants to the (Aviva) treatment group and 195 participants to the active control (sham) group and expect to have suicide attempt data for 100% of these participants. We investigated several reasonable variations of the group sequential design and determined that the following is most reasonable. We will test at the 0.025 significance-level (one-sided). The group sequential design has 3 interim sequential tests (4 total looks including final analysis). The looks will occur when 60%, 75%, 90% and 100% of the expected events (i.e., suicide attempts) have occurred. The O'Brien-Fleming spending function is used to determine the effectiveness test boundary. The group sequential design boundaries (on a z scale) are presented in Attachment C.

The power of this GSD is 90%.

Survival analyses will be conducted using the log-rank test for the effectiveness of the intervention on the time to the first suicide attempt after randomization while controlling for censoring effects due to the differential length of follow-up or the completion of follow-up without a suicide attempt. Time to suicide attempt will be measured by calculating the total number of days from enrollment to the first suicide attempt. For participants without a suicide attempt, the total number of days since enrollment to the last assessment will be calculated.

While every effort will be made to track suicide attempts (SA), there may be some missing data. Consistent with standard statistical procedures, missing data are included in the time-to-event analysis as censored observations, with the censoring time at the last contact time with the patient (Friedman et al., 2015).

Estimates of participants making at least 1 subsequent suicide attempt before study end and reattempt-free probabilities at any time point will be derived by the Kaplan-Meier method. The

between-group difference in the proportion of participants making at least 1 repeat suicide attempt by 104 weeks will be evaluated using the asymptotic properties of the Kaplan-Meier estimators of survival probabilities. Although we do not anticipate dropout (because suicide attempt data can be collected via multiple means), this method was chosen to account for dropouts based on the Intent-to-Treat (ITT) principle.

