### 7.5 RANDOMIZATION CRITERIA

Participants who meet the eligibility criteria will be assigned a participant number and will then be randomly assigned to the Aviva + TAU or sham + TAU groups. A computerized modified minimization randomization procedure within the electronic Case Report Forms (eCRFs) will be used. Eligible participants will be randomized based on study site, sex, race/ethnicity and whether they have had no attempts, single attempts or multiple suicide attempts. This adaptive randomization method has been shown to be superior to stratified randomization in producing balance for separate prognostic variables, particularly when the number of strata is large compared with the number of subjects. Once the participant is randomized the site staff will make sure that the participant has properly loaded Aviva **or** sham app onto his/her phone. The PI or designee will confirm that the app has been downloaded and, if the participant is having difficulty, assist them beginning the onboarding session.

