The sensitivity analyses will proceed in the following manner: the primary analysis will be repeated in the per-protocol population and the Cox proportional hazards model will be carried out on the ITT population to investigate the robustness of the finding for suicide attempt in the presence of potentially important factors such as sex, race/ethnicity, and site. The ITT will be used for the primary and secondary endpoint analysis either here or in the sections above where each is discussed. Associated Wald tests will be conducted using a significance level of .05 (2-sided) to test the null hypothesis that the two time-to-event distributions are the same for the Aviva and sham groups at any time point. We will conduct subgroup analysis based on the stratification factors used in our randomization (sex, race/ethnicity and previous suicide attempt history [i.e., whether participants had no suicide attempts, a single attempt or multiple suicide attempts] and investigative site). We will include sex, race/ethnicity because differences in rates (or increases in rates) have been observed for each. Regarding sex, the age adjusted suicide death rate for males (22.79 per 100,000) is higher than the rate for females (6.18 per 100,000; CDC, 2020). For race/ethnicity, American Indian/Alaska Native adults are at highest risk for past-year suicide attempts, followed by Black and Hispanic adults (CDC, 2020). Lastly, while all efforts will be made to standardize procedures across sites, it is possible that site differences may emerge. Thus, we will examine whether there are any treatment differences based on sites. Lastly, previous suicide attempt history is a strong predictor of future suicide attempts.

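### The primary log-rank test is not stratified by attempt history, a minimization factor the protocol calls strongly predictive; stratifying would recover a little power at no cost

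*Protocol*

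**What the plan says.** - **Allocation (Section 7.5).** A modified minimization procedure is used: "Eligible participants will be randomized based on study site, sex, race/ethnicity and whether they have had no attempts, single attempts or multiple suicide attempts".
- **Primary test (Section 11.1.4, repeated in the synopsis).** "Survival analyses will be conducted using the log-rank test for the effectiveness of the intervention on the time to the first suicide attempt". The only thing the text says is controlled for is censoring. No strata or covariates appear.
- **Sizing (Section 11.1.3 and Attachment C).** The calculation is for a two-group log-rank test, also without strata.
- **Sensitivity model (Section 11.3).** A Cox model on the ITT population examines robustness "in the presence of potentially important factors such as sex, race/ethnicity, and site". Of the four minimization factors, attempt history is the only one not named.
- **Subgroups (Section 11.3).** All four factors define subgroups. For history the stated reason is that "previous suicide attempt history is a strong predictor of future suicide attempts".
- **Poolability (Section 11.4).** Cox models look at site, race, sex and age. The section adds that center is to be handled as a nuisance factor in the analyses, without saying which analyses or how.

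**The concern.** Minimization removes most of the chance imbalance between arms on the balanced factors. A test that ignores those factors still computes its variance as if that imbalance could occur. If a factor is prognostic, the variance is too large, so the test falls below its nominal level and loses power. The marginal hazard ratio also lies nearer 1 than the hazard ratio within levels of the factor.

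Of the four factors, the protocol itself singles out attempt history as a strong predictor of future attempts, and the eligibility criteria mix recent attempters with patients admitted for ideation, so history will vary. It therefore shapes allocation and subgroups but is named in no effectiveness model. At stake is some power in a trial that rests on 52 events.

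**Working it through.** **1. The plan's own figures.** The inputs are in Section 11.1.3 and Attachment C: "A total sample size of 391 (with 52 events) is required to achieve 90% power to detect a hazard ratio of 0.3826"; "survival rates of 0.9240 in the Aviva group [group 1] and 0.8124 in sham app group [group 2] at 18 months"; "total study time is 104 weeks (24 months) with 52 weeks (12 months) accrual". Section 11.1.4 gives the level: "We will test at the 0.025 significance-level (one-sided". Attachment C gives a drift of 3.4387 and monthly hazards of 0.0115 (sham) and 0.0044 (Aviva).

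- Events needed = 4 × drift² / ln(HR)² = 4 × 3.4387² / ln(0.3826)² = 51.24, rounded up to 52.
- Probability of an event by month 24 with uniform 12-month accrual = 1 − [exp(−12λ) − exp(−24λ)] / (12λ). This gives 195 × 0.1863 = 36.3 for sham and 196 × 0.0760 = 14.9 for Aviva, 51.2 in total. Rounded up by arm, these are the stated 37 and 15.
- The stated efficacy bounds give alpha 0.0250 with futility ignored. Power is 0.900 with the futility bounds applied.

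The size, alpha and power therefore reproduce.

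**2. Effect of stratifying, under minimization.** Simulation of 3,000 trials per scenario with N = 391, biased-coin minimization on the four factors, 12-month accrual, data cut at month 24, sham 18-month survival 0.8124, and the final bound of 2.0748 (nominal 0.0190) applied once. Assumed, because the documents do not give them: one third of patients at each history level; hazard ratio R for multiple versus no prior attempts, with √R for a single attempt; the other factors not prognostic. Each cell shows the plain test, then the test stratified by history.

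| R | Type I error | Power at HR 0.3826 | Power at HR 0.50 |
|---|---|---|---|
| 1 | 0.016, 0.016 | 0.894, 0.893 | 0.686, 0.685 |
| 2 | 0.019, 0.020 | 0.895, 0.896 | 0.673, 0.676 |
| 4 | 0.015, 0.019 | 0.891, 0.897 | 0.670, 0.689 |
| 8 | 0.015, 0.020 | 0.880, 0.896 | 0.636, 0.673 |

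The simulation standard error is about 0.0025 for the error rates. A Cox model adjusted for history gave power close to that of the stratified test.

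**3. A larger run at 52 events.** 12,000 trials per scenario, N = 390, allocation balanced within history level, same bound, both tests on the same data.

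| R | Type I error (%) | Power at HR 0.3826 (%) | Power at HR 0.50 (%) |
|---|---|---|---|
| 2 | 1.84, 1.88 | 89.9, 89.7 | 65.1, 65.4 |
| 4 | 1.78, 1.88 | 89.2, 90.0 | 62.8, 64.2 |
| 8 | 1.47, 1.81 | 88.2, 89.9 | 61.3, 64.7 |

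The standard error of an error rate near 1.9% is √(0.019 × 0.981 / 12,000) = 0.12 points. The plain test is thus clearly below nominal at R = 8: (1.90 − 1.47) / 0.12 is about 3.5 standard errors. At R = 4 it is only about one standard error below. The power gains are firmer because the tests are paired. At R = 4 and HR 0.50, 249 trials were significant only with stratification and 73 only without: (249 − 73) / √(249 + 73) = 9.8.

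**4. How far to stratify.** With 4 to 8 sites, 2 sexes, an assumed 2 to 5 race/ethnicity groups and 3 history levels, joint stratification makes 4 × 2 × 2 × 3 = 48 to 8 × 2 × 5 × 3 = 240 cells for 52 events. History alone makes 3.

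**The case against.** The strongest reply is that nothing here is wrong. The trial is sized and analysed with the same plain log-rank test, and that test protects the type I error. **This stands**, and it limits the point to efficiency.

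- **Size of the gain.** At the design hazard ratio it is under 1 point unless the history gradient is steep. With a 30/30/40 split and hazards of 1:1.7:3 and 1:3:6, power at 0.3826 moved only from 90.1% to 90.5% and from 89.0% to 90.0%. This stands.
- **Small strata at the first look.** With hazards of 1:3:6, the no-attempt stratum averages under 3 events at the first look. A check at 31 events nevertheless found that the stratified test held its level. One run at 1:3:6 gave the stratified test 2.7% error at Z = 1.96, but 1.96 is not one of the protocol's bounds. At the final bound of 2.0748 the stratified error was 1.6% to 2.0% in the tables above, against a nominal 1.9%.
- **The Cox list is open.** It is introduced as examples, and a full covariate list commonly belongs in the SAP. A reader might infer that history is deliberately excluded; the text supports only that it is not named. The primary test is different, because the protocol itself fixes it.
- **Broader readings.** A reader might infer that every minimization factor is ignored. Section 11.3 names three of them in the Cox model, and Section 11.4 speaks of center as a nuisance factor. A reader might also extend the point to the SSI analysis. The Section 11.1.5 model already has site and baseline SSI, and no gain from adding history was shown.

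**Conclusion.** The point holds as a small, free improvement. The primary test as written makes no use of the one minimization factor that the protocol calls a strong predictor. A reader might infer that the significance level or the sample size is therefore unsound. The documents do not support that: alpha, 52 events, N = 391 and 90% power all reproduce, and the plain test errs only toward conservatism.

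Over both runs, with R from 2 to 8, stratifying by history gains about 0 to 2 points of power at HR 0.3826 and 0 to 4 points at HR 0.50. Those ranges rest on the assumed equal thirds and history gradients, neither of which the documents give. At R = 2 or below the gain is essentially nil, although the protocol's own description of history argues against so weak an effect.

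Separately, the Section 11.4 statement on center and the unstratified primary test need to be reconciled.

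**What to change.** Amend the wording before the first look, so that the choice of primary test cannot be questioned in the light of interim data:

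1. In Section 11.1.4 and the synopsis, make the primary test a log-rank test stratified by attempt history (none, single, multiple), and take the reported hazard ratio from a Cox model stratified the same way. Do not stratify by all four factors jointly.
2. In the Section 11.3 Cox sensitivity model, name attempt history beside sex, race/ethnicity and site.
3. In Section 11.4, state whether and how center enters the primary analysis.

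The SSI model needs no change on this account. The cost is protocol text only. Attempt history is already collected for every participant in order to randomize, and the number of events, the sample size and the stated bounds stay as they are.
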